## Abstract

**Background::**

Thyroidectomy has been considered an effective method to treat thyroid cancer. However, about 20% of patients have psychological distress before surgery. Psychological distress is considered common mental illnesses and it has been reported that the patients who suffer psychological distress have poor clinical outcomes than the patients without psychosocial disorder. Therefore, we design this randomized controlled study to explore the effect of psychological nursing intervention against quality of life and psychological distress of the patients with thyroid cancer.

**Method::**

The trial will be conducted from September 2020 to December 2020 at Wuhan Fourth Hospital on the basis of the International Council for Harmonisation's Good Clinical Practice Guidelines and the principles of the Helsinki Declaration. The study was authorized via the Research Ethics Committee of the Wuhan Fourth Hospital (Approval number: 20200721-046). This study is a single-center, randomized, 2-arm, evaluator-blinded clinical trial. In all, 90 patients with thyroid cancer undergoing thyroidectomy will be enrolled in this study. The inclusion criteria includes: patients aged between 20 and 60 years old; ASA I-II classification; normal platelet coagulation and count function. The exclusion criteria contains: people with the intellectual and cognitive impairment (behavioral-cognitive intervention); BMI above 35 kg/m^2^; the history of renal and hepatic dysfunction; and patients refuse to participate in this study. Both the patients in psychological intervention group and control group should receive the routine care, while the psychological intervention group also needs to receive the additional proper psychological nursing interventions. The emotional disorders are detected with the Chinese version of Profile of Mood States-Brief. And the patients’ life quality is evaluated with the European Organization for Research and Treatment of Cancer Quality of Life Questionnaire-Core Questionnaire (QLQ-C30, version 3.0). All the data are collated into Microsoft Excel 2010 and analyzed with SPSS 12.0 (IBM).

**Results::**

It is assumed that psychological nursing intervention could alleviate the psychological distress of patients with thyroid cancer and improve their quality of life.

**Conclusion::**

This study can provide the reliable evidence regarding the influence of psychological nursing intervention against the life quality and psychological distress of the patients with thyroid cancer.

**Trial registration::**

This study protocol is registered in Research Registry (researchregistry5937).

## Introduction

1

Due to the rapid rise in incidence of thyroid cancer, it is now recognized as a major public health problem globally.^[1–3]^ It is the most familiar kind of endocrine malignancy and it causes more deaths than all other endocrine cancers combined. In the United States, from 1975 to 2009, the annual incidence increased from 14.9 per 100,000 to 14.3 per 100,000, almost tripling.^[4]^ Similarly, in the People's Republic of China, the incidence increased 2.4 times from 1988 to 2009, with 6.0% average annual growth rate.^[5]^ Differentiated thyroid carcinoma originates from the thyroid follicular cells and consists of follicular histological and papillary types, accounting for 90% of all the thyroid cancers.^[6]^

Thyroidectomy has been considered an effective method to treat thyroid cancer.^[7]^ However, about 20% of patients have psychological distress before surgery. Psychological distress is considered common mental illnesses and it has been reported that the patients who suffer psychological distress have poor clinical outcomes than the patients without psychosocial disorder.^[8]^ Even if we consider their importance, only few research has tried to manage the disorder. It is necessary to construct proper communication channels with the patients, establish positive harmonious relationship, and encourage cooperation, thus guiding patients to face the reality of the disease bravely.

Psychological nursing intervention is to carry out psychological nursing guidance for the patients, so that they can keep peace of mind, and then cooperate with the relevant treatment and nursing actively.^[9]^ Literature reports that in the clinical study, the effective psychological intervention can help to improve the patients’ psychological quality, and then enhance their life quality, which possesses great clinical significance.^[10]^ However, it is remained controversial regarding the effect of psychological nursing intervention in patients with thyroid cancer due to the small published articles. Therefore, we design the randomized controlled research to explore the effect of psychological nursing intervention against the life quality and psychological distress of the patients with thyroid cancer.

## Methods

2

### Study design

2.1

The trial will be conducted from September 2020 to December 2020 at Wuhan Fourth Hospital on the basis of International Council for Harmonisation's Good Clinical Practice Guidelines and the principles of the Helsinki Declaration. The research was authorized via the Research Ethics Committee of the Wuhan Fourth Hospital (Approval number: 20200721–046) and registered with in research registry (researchregistry5937). This study is a single-center, randomized, 2-arm, evaluator-blinded clinical trial. In all, 90 patients with thyroid cancer undergoing thyroidectomy will be enrolled in this study. The recruited patients are given the written informed consent before enrollment. The inclusion criteria contains: aged 20 to 60 years; ASA I-II classification; normal platelet coagulation and count function. The exclusion criteria contains: people with the intellectual and cognitive impairment (behavioral-cognitive intervention); BMI above 35 kg/m^2^; the history of renal and hepatic dysfunction; and patients refused to participate in this study.

### Psychological nursing intervention

2.2

Both the patients in psychological intervention group and control group should receive the routine care, while the psychological intervention group also needs to receive the additional proper psychological nursing interventions. The contents of psychological nursing intervention are illustrated in Table 1.

**Table 1 T1:**
[figure not shown]
Contents of the psychological nursing intervention.

### Psychological distress

2.3

The emotional disorders are detected with the Chinese version of Profile of Mood States-Brief.^[11]^ It involves 6 subscales (anger, fatigue, tension, depression, vigor, and confusion). Each subscale contains some adjectives (e.g., panic, unpleasant, sleepy, tired, and so on). There are 65 adjectives in total. And the items in each subscale are mixed. There are 5 levels for each answer: 0 represents no; 1 is a little; 2 represents media; 3 is a lot; and 4 represents very much. Total mood disorders = the negative mood score (sum of anger, depression, stress, confusion, and fatigue) minus the positive mood score (sum of self-esteem and vitality) and then plus the constant (100). A higher score corresponds to a more negative emotional state. The anxiety and depression are measured through utilizing the Hospital Anxiety and Depression Scale. The table consists of 2 subscales of depression and anxiety, each of which involves 7 questions about depression and anxiety. Each question has 0 to 3 points and 4 answers. The scores of each subscale of anxiety and depression are 0–7+ that represents asymptomatic; 8–10+ points that is suspicious; and 11–21+ points that represents definitely existed; when scoring, the starting point is 8 points. Both symptomatic and suspicious are positive.

### Quality of life

2.4

The patients’ life quality is evaluated with the European Organization for Research and Treatment of Cancer Quality of Life Questionnaire-Core Questionnaire (QLQ-C30, version 3.0).^[12]^ It is divided into 3 symptom fields (pain, fatigue, nausea, vomiting), 5 functional fields (cognitive function, role function, physiological function, social function, and emotional function), 1 area of quality of life/entire health status, as well as 6 separate items (each as a field). The scoring rules explicitly state that higher scores for the overall health conditions and functional areas are associated with better quality of life and functional status.

### Statistical analysis

2.5

SPSS Sample Power 3.0 software (IBM, Armonk, NY) is used to calculate the sample size. For the purpose of this study, the baseline data of outcome variables are utilized as covariate, and the needed sample size is estimated to be 45 participants in each group via independent-samples one-way analysis of covariance (ANCOVA) to detect the effects of power of 0.8 and alpha of 0.05. All the data are collated into Microsoft Excel 2010 and analyzed with SPSS 12.0 (IBM). The comparison of baseline characteristics of the patients between these 2 groups is carried out through utilizing the *χ*^2^ test for categorical data or the independent-sample *t* tests for continuous data. Intention-to-treat analysis is used for the outcome assessments. The linear mixed patterns are utilized to assess the difference of life quality and psychological distress. The *P* < .05 is regarded as statistically significant.

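### No primary outcome is named among about 24 scores, the sample size is tied to none of them, and one unadjusted P < .05 covers them all

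*Protocol article*

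**What the plan says.** All references are to the protocol article.

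- **Section 2.3, Psychological distress.** The mood-state scale has six subscales and a total. A second instrument follows: "The anxiety and depression are measured through utilizing the Hospital Anxiety and Depression Scale". It gives two subscale scores.
- **Section 2.4, Quality of life.** On the QLQ-C30: "It is divided into 3 symptom fields (pain, fatigue, nausea, vomiting), 5 functional fields". One global area and six single items, each counted as a field of its own, complete it. No sum score over the fields is defined.
- **Section 2.5, Statistical analysis, sample size.** "the needed sample size is estimated to be 45 participants in each group", by ANCOVA, "to detect the effects of power of 0.8 and alpha of 0.05". The only link to an outcome is that "the baseline data of outcome variables are utilized as covariate".
- **Section 2.5, outcome analysis.** "The linear mixed patterns are utilized to assess the difference of life quality and psychological distress". The decision rule is that P "< .05 is regarded as statistically significant".

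No section calls a score primary, ranks the scores, or says what result would make the trial positive.

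**The concern.** A significance threshold controls the error rate of a conclusion only if the test that decides it is fixed in advance. Here the reader knows two domains, three instruments and one threshold, but not which score decides. The choice can be made after the results are seen, and the more scores there are to choose from, the more likely it is that one crosses the threshold by chance.

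The sample size has the same gap. Power of 80% is a property of one test on one outcome with one assumed effect. It cannot be attached to a plural set of outcomes, so nobody can check whether 45 per group suits the score that is finally reported as the main one.

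A multiplicity procedure may reasonably sit in an analysis plan that is not shown. The primary outcome is different. It belongs in the protocol, and the sample size calculation printed in this article has to rest on it.

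**Working it through.** **1. The plan's own figure.** Forty-five per group cannot be reproduced, because section 2.5 gives no effect size, standard deviation or baseline correlation. Solving backwards for the standardised difference *d* (two-sided 0.05 assumed, since sidedness is not stated; no covariate):

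*d* = (1.960 + 0.842) × √(2/45) = 0.59.

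With ANCOVA and assumed baseline correlations of 0.3, 0.5 and 0.7, the detectable *d* is 0.57, 0.52 and 0.43. Nothing in the article says to which score any of these applies.

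**2. Count of scores.**

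- Mood-state scale: 6 subscales + 1 total = 7
- HADS: 2
- QLQ-C30: 3 + 5 + 1 + 6 = 15
- Total: 7 + 2 + 15 = 24

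The formula for the mood total also uses a self-esteem score that is not among the six listed subscales. Counting it gives 25.

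**3. All 24 tested, independent, no true effect.**

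- At least one P < .05 in either direction: 1 − 0.95^24 = 0.708 (25 scores: 0.723)
- Expected number of false positives: 24 × 0.05 = 1.2
- At least one in favour of the intervention: 1 − 0.975^24 = 0.455

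**4. All 24 tested, correlated.** The scores cannot be independent; the mood total is built from its own subscales. The article gives no correlations, so a common correlation ρ between test statistics is assumed. With *U* standard normal,

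- *a*(*U*) = Φ((1.96 − √ρ·*U*)/√(1 − ρ))
- *b*(*U*) = Φ((−1.96 − √ρ·*U*)/√(1 − ρ))

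the two chances are 1 − E[(*a* − *b*)^24] (either direction) and 1 − E[*a*^24] (in favour).

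| Assumed ρ | Either direction | In favour |
|---|---|---|
| 0 | 71% | 46% |
| 0.3 | 59% | 31% |
| 0.5 | 46% | 23% |
| 0.7 | 31% | 16% |
| One test only | 5% | 2.5% |

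**5. Only four summary scores tested** (mood total, two HADS scores, global health), independent.

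- Either direction: 1 − 0.95^4 = 0.186
- In favour: 1 − 0.975^4 = 0.096

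**6. A favourable false positive required in both domains,** with 9 distress and 15 quality-of-life scores tested. If independent:

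(1 − 0.975^9) × (1 − 0.975^15) = 0.204 × 0.316 = 0.064.

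Under the model of step 4 this is E[(1 − *a*^9)(1 − *a*^15)], which gives 8.9%, 8.6% and 7.4% at ρ = 0.3, 0.5 and 0.7.

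**The case against.** The strongest reply is that the article does not say every score is tested. Section 2.5 names two domains, while sections 2.3 and 2.4 describe how the instruments are built. A mood total and a global health area exist, so an analysis of summary scores is possible. This stands, and it is why the 24-score figures are conditional. It does not remove the problem, because nothing in the article selects the summary scores either.

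Several stronger readings are tempting but not supported:

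- **A positive trial is likely by chance alone.** The 71% needs 24 independent tests and counts results against the intervention. The chance of a favourable false positive stays below 50% at every correlation shown.
- **Any single significant score would establish the claim.** The Results section expects benefit on distress and on quality of life together. For that conjunction the rate is 6 to 9% with all 24 scores tested. On the narrowest reading (a favourable result on one of three distress summary scores and on global health) it falls below the nominal level: if independent, (1 − 0.975^3) × 0.025 = 0.0018. The article commits to no such rule, so this reading cannot be relied on.
- **Repeated visits multiply the tests.** Linear mixed models can combine visits into one comparison, and the article does not say that each visit is tested.
- **The abstract contradicts the body.** For distress the abstract says only that "The emotional disorders are detected with the Chinese version of Profile of Mood States-Brief" and omits the HADS. That is condensation, not contradiction.

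Finally, multiplicity rules and visit timing may stand in documents that are not shown. That is a fair answer on those two details, but not on the primary outcome.

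**Conclusion.** The point holds in this form: about 24 scores are listed, none is primary, the sample size rests on no identified score, and the one stated threshold is unadjusted. Confidence in that is high, because it can be read directly from sections 2.3 to 2.5.

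The size depends on what is tested and on how success is judged, and the article fixes neither. If any favourable score counts, the chance under no effect runs from about 10% (four independent summary scores) to 46% (24 independent scores), and the 24-score figure is 16 to 31% at correlations of 0.7 to 0.3. If both domains must show one, with all scores tested, it is 6 to 9%. These compare with 2.5% for one pre-specified two-sided test. They assume two-sided testing, no true effect on any score and one common correlation. The defect should be corrected before analysis, since naming the outcome afterwards gives no protection.

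**What to change.** Before any data are analysed:

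1. Name one primary score at one assessment time, for example the mood-state total, and test it at two-sided 0.05.
2. Tie the stated sample size and power to that score.
3. Test QLQ-C30 global health status next, at 0.05, only if the primary is significant.
4. Report all other scores as secondary, either with confidence intervals and no claim of significance, or with Holm-adjusted P values.

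This takes protocol wording only. The primary keeps the full alpha, so multiplicity calls for no extra patients. By contrast, a Bonferroni split over 24 scores would set the threshold at 0.05/24 = 0.0021. At *d* = 0.59 that leaves about 39% power with 45 per group, or needs about 89 per group. The price of the proposed change is that a secondary score can no longer carry the conclusion alone.

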## Results

3

It is assumed that psychological nursing intervention could alleviate the psychological distress of patients with thyroid cancer and improve their quality of life.

## Discussion

4

Nowadays, it is extensively believed that the psychological factors play an important role in the process of canceration, meaning that the cancer patients may be more likely to report psychological symptoms such as increased stress, depression and anxiety, etc. unconsciously or consciously than the patients with benign tumors.^[13,14]^ In the modern medicine, education in health has become a significant part of treatment. For example, psychological care is utilized to intervene in the lives of patients with mental health problems, thereby improving the treatment compliance. More and more studies have emphasized the importance of psychological nursing intervention in reducing psychological distress in patients with cancer.^[15,16]^ At the same time, the nurses should try to reduce any adverse stimulation, eliminate harmful psychological barriers, and analyze the emotional changes and thinking process of patients, encourage the patients to express their true feelings, so that they can express their negative emotions safely.^[17,18]^ Our current work is the first clinical randomized controlled trial to explore the effect of psychological nursing intervention against quality of life and psychological distress of the thyroid cancer patients. These findings must be replicated in more research centers and in larger samples, and evaluated over longer periods of follow-up, before final conclusions can be drawn.

## Conclusion

5

This study can provide the reliable evidence regarding the influence of psychological nursing intervention against the life quality and psychological distress of the patients with thyroid cancer.

## Abbreviations

Abbreviation: QCQ = questionnaire-core questionnaire.
